# 7. ASSESSMENT OF SAFETY

## 7.1 Serious Adverse Event

### 7.1.1 Definition of Serious Adverse Event

A serious adverse event (experience) or reaction is any untoward medical occurrence that at any dose:

- 1) results in death
- 2) is life threatening

NOTE: The term “life-threatening” in the definition of “serious” refers to an event in which the patient was at risk of death at the time of the event; it does not refer to an event, which hypothetically might have caused death if it were more severe.

- 3) requires inpatient hospitalization or prolongation of existing hospitalization

---

 Complications occurring during hospitalisation are AEs and are SAEs if they cause prolongation of the current hospitalisation. Hospitalisation for elective treatment of a pre-existing non worsening condition is not, however,  
 Clinical Study Protocol  
 Version: Final revised  
 Date: 2012-03-27

- 4) results in persistent or significant disability/incapacity, or
- 5) is a congenital anomaly/birth defect

In addition, medical and scientific judgment is required to decide if prompt notification is required in other situations, i.e. any event which the investigator regards as serious that did not strictly meet the criteria above but may have jeopardized the subject or required intervention to prevent one of the outcomes listed above, or which would suggest any significant hazard, contraindication, side effect or precaution that may be associated with the use of the drug.

### ***7.1.2 Reporting of Serious Adverse Event***

The investigator must report any SAE occurring between the treatment with study drug and completion of 3-month follow-up after last treatment, whether or not considered related to study drug to the sponsor.

Pregnancies occurring during the study, although not SAEs, should be reported using the SAE reporting procedures.

The SAE should be reported by telephone and/or fax **within 24 hours** following knowledge of the event by the investigator for the attention of **[name]**:

[contact]  
[contact]

The investigator should not wait to receive additional information to fully document the event before notifying a SAE, although additional information may be requested. Where applicable, information from relevant laboratory results, hospital records and autopsy reports should be obtained. The investigator is also required to submit follow-up reports until such time as the AE has resolved or in the case of permanent impairment, until the AE stabilizes.

Instances of death, congenital abnormality or an event that is of such clinical concern as to influence the overall assessment of safety, if brought to the attention of the Investigator at any time after cessation of study medication and linked by the Investigator to this study, should be reported.

The sponsor will report the SAE to the relevant authority within the required timeframe, depending on the local regulations, electronically where possible. Sponsor will report all serious and unexpected adverse drug reactions in an expedited fashion to all concerned investigators. Sponsor together with the investigators are responsible for reporting serious and unexpected adverse drug reactions to the Independent Ethics Committees (IECs) or Institutional Review Board (IRB), where required.

Details of SAEs will also be reported on the adverse event pages in the CRF.

---

considered an AE. The details of such hospitalisations must be recorded on the medical history/physical examination page of the CRF.

 An AE is incapacitating or disabling if it results in a substantial and/or permanent disruption of the patient's ability to carry out normal life functions.

Clinical Study Protocol  
Version: Final revised  
Date: 2012-03-27

Sponsor: NTNU  
Study Code: NTNU 2011-1  
EudraCT No: 2011-004797-28 NO 20120327

## **7.2 Adverse Event**

### ***7.2.1 Definition of Adverse Event***

An adverse event (AE) is any untoward medical occurrence in a patient or clinical investigation subject administered a pharmaceutical product and which does not necessarily have a causal relationship with this treatment.

An adverse event can therefore be any unfavourable and unintended sign (including an abnormal laboratory finding), symptom, or disease temporally associated with the use of a medicinal (investigational) product, whether or not related to the medicinal (investigational) product.

All events occurring after the subject has signed the study consent form but before receiving the drug/procedure will be registered as clinical symptoms at baseline.

### ***7.2.2 Reporting of Adverse Event***

Local phototoxic reactions like pain, erythema and pustular eruption, and any other adverse events related to the treatment according to the investigator will be recorded in the CRF.

All reported AE's will be followed up until resolved or as clinically required.

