### 5.6.2 Safety follow-up

In case of any adverse event patients should take contact with their G.P. or the local hospital for further consultation. Adverse event will be recorded in the CRF at the follow-up visits if related to treatment, according to the investigator

Follow-up:

| Treatment regime/ lesions                                                              | Follow-up/ months after treatment  |
|-----------------------------------------------------------------------------------------------|-------------------------------------------|
| Regime 1/ all lesions                                                                         | 3 months after 1 treatment session        |
| Regime 1/ lesions with non-complete response 3 months after first session with a re-treatment | 3 months after 2 treatment session        |
| Regime 1/ all lesions in complete response                                                    | 12 months after 1 or 2 treatment sessions |
| Regime 1/ all lesions in complete response                                                    | 36 months after 1 or 2 treatment sessions |
| Regime 2/ all lesions                                                                         | 3 months after 2 treatment session        |
| Regime 2/ all lesions in complete response                                                    | 12 months after 2 treatment sessions      |
| Regime 2/ all lesions in complete response                                                    | 36 months after 2 treatment sessions      |

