### ***7.2.3 Assessment of Adverse Event***

Adverse events may be reported spontaneously by the subject or elicited through open (non-leading) questioning during the study. As far as possible, all AE's must be described by their duration (start and stop date), severity (mild, moderate, or severe; see Section 0), relationship to treatment (yes, uncertain, no; see Section 0), and according to the need of other specific therapy.

Localization of AE's will be recorded as "treatment area" or "non-treatment area"(see Section 0). The onset of AE's will be classified relative to the stage of treatment as described in Section 0.

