### ***7.2.5 Relationship of Adverse Event to new treatment regime using MAL-PDT***

The investigator's opinion of the relationship of the AE(s) to the investigational drug, will be categorized as "yes," "uncertain," or "no."

- No: An AE, which after careful examination at the time of evaluation, is judged to be clearly and incontrovertibly due to extraneous causes (disease, environment, etc) and which does not meet the criteria for drug relationship and/or device relationship listed under uncertain or yes.
- Uncertain: An AE, for which after careful examination at the time of evaluation, the connection with the test drug administration or illumination appears unlikely, but cannot be ruled out with certainty.
- Yes: An AE, for which after careful examination at the time of evaluation, the connection to the test drug administration or illumination appears, with a high degree of certainty, to be related to the test drug and/or device.

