### **8.2.3 Safety**

The reported adverse events (including local reactions) will be coded according to MedDRA terminology. The number and percentages of subjects with at least one adverse event, and the relationship will be tabulated. Occurrence of particular adverse events (by body system and preferred MedDRA term) and their severity and relationship will be summarized using counts and percentages of subjects.

The erythema and pustular eruption scores with 4 categories will be summarized by treatment regime group and time point using count and percent.

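### Non-serious adverse events other than local phototoxic reactions reach the CRF only if already judged treatment-related, which conflicts with the protocol's own relationship rating and its safety table

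*Protocol*

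**What the plan says.** The Protocol states the recording rule twice. Section 5.6.2: "Adverse event will be recorded in the CRF at the follow-up visits if related to treatment, according to the investigator". Section 7.2.2 names local phototoxic reactions (pain, erythema and pustular eruption are its examples) for recording and then adds that "any other adverse events related to the treatment according to the investigator will be recorded in the CRF".

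Other sections are written as if events are recorded first and judged afterwards:

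- Section 7.2.1 defines an AE as an untoward occurrence "whether or not related to the medicinal (investigational) product".
- Section 7.2.3 lists what must be described for all AEs as far as possible, including "relationship to treatment (yes, uncertain, no; see Section 0" (the cross-reference is broken; section 7.2.5 is evidently meant).
- Section 7.2.5 says the "relationship of the AE(s) to the investigational drug, will be categorized as" yes, uncertain or no, and defines *no* as an event "judged to be clearly and incontrovertibly due to extraneous causes".
- Section 8.2.3: "The number and percentages of subjects with at least one adverse event, and the relationship will be tabulated".

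SAEs follow a separate rule. Section 7.1.2 requires them to be reported whatever their cause, up to completion of the 3-month follow-up after the last treatment, and also entered on the AE pages of the CRF.

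**The concern.** A causality scale that is completed after recording cannot work as intended when recording itself depends on causality. Those who read the section 8.2.3 table would take it to show all AEs, divided by how likely they were to be caused by treatment. For a large class of events it would show only those that had already passed a relatedness judgement.

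This is a rule for data collection, so a statistical analysis plan cannot repair it: events that were never entered cannot be analysed. AEs are also a declared outcome. Section 3.1 promises to report them for both regimes from the first treatment until 3 months after the last, and section 1.2 names less discomfort and fewer adverse reactions among the hoped-for benefits of the simpler regime.

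**Working it through.** The point involves no sample size, rate or margin, and the plan gives no figure to reproduce. The check is to follow each class of AE through the recording rules (5.6.2, 7.2.2, 7.1.2) and then through the rating and tabulation rules (7.2.3, 7.2.5, 8.2.3).

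| Class of event | Does it enter the CRF? | Can it be rated and tabulated? |
|---|---|---|
| SAE, any cause | Yes, under 7.1.2 | Yes, including as *no* |
| Local phototoxic reaction | Yes, named in 7.2.2 | Yes; treatment-related by its nature |
| Other non-serious AE, judged *yes* | Yes, under 5.6.2 and 7.2.2 | Yes |
| Other non-serious AE, judged *uncertain* | Unclear | Depends on how the site reads 'related' |
| Other non-serious AE, judged *no* | No | No |

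Four consequences follow.

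1. **The *no* category.** Section 7.2.5 defines it for any AE, but the last row of the table never reaches the CRF. The category can hold only SAEs.

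2. **The *uncertain* category.** Its definition in 7.2.5 describes a connection that seems unlikely but cannot be excluded. An investigator could fairly decide that such an event is not related and leave it out. However, the definition of *no* refers to relationship criteria listed under both *uncertain* and *yes*, so another investigator could fairly decide that *uncertain* counts as related and record it. The text supports both readings.

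3. **The any-AE count in 8.2.3.** It would cover phototoxic reactions, other related events, possibly some uncertain ones, and all SAEs. That is narrower than AEs as 7.2.1 defines them, and the table carries no label saying so.

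4. **Who applies the filter.** Sections 5.6.2, 7.2.2 and 7.2.5 give the relatedness judgement to the investigator. Section 5.2 calls the study open. Section 3.3 provides a blinded dermatologist, whose stated task is to evaluate the lesions. No section says that the person judging AE causality is unaware of the regime.

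The firm conflict is between 5.6.2 and 7.2.2 on one side and 7.2.3, 7.2.5 and 8.2.3 on the other. The difference from 7.2.1 is a mismatch of coverage: a recording rule may be narrower than a definition without contradicting it.

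**The case against.** The case against giving this much weight is substantial.

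- **Coverage is better than the two sentences suggest.** A reader might infer that only treatment-related AEs are ever recorded and that the *no* row must be empty. Section 7.1.2 rules that out, because unrelated SAEs go onto the AE pages. Phototoxic reactions are also named for recording. This stands, and it confines the point to other non-serious events.
- ***Uncertain* may be covered.** The wording of *no* in 7.2.5 can be read as placing *uncertain* among the relationship criteria. This stands as a possible reading, so it cannot be said that such events are lost. It does not remove the need to state the rule.
- **The side-effect claim rests mainly on events that are recorded.** The reactions expected in sections 1.2 and 10.3 are chiefly local ones, such as pain, erythema and inflammation, and 8.2.3 summarises erythema and pustular eruption by regime and time point. A reader might infer that the comparison of side effects is undermined. The documents do not support that: events clearly due to other causes say little about discomfort from treatment, the benefit in 1.2 is a conditional expectation, and the safety analysis is descriptive with no stated hypothesis.
- **Unblinded filtering is an inference.** Lesions are randomised after the first illumination (5.2), so reactions up to that point precede allocation. Section 8.1 has AEs noted at the 3-month visit, where the blinded dermatologist evaluates lesions, and calls the design both open label and controlled blinded. Who judges causality there is not stated. The opportunity for bias is real; its occurrence is not shown.
- **Fuller recording would not yield a clean comparison by regime.** Under 5.2 a patient with several lesions can receive both regimes, while 8.2.3 counts subjects. A systemic event in such a patient cannot be assigned to one regime. This stands.
- **Restricted collection can be a legitimate choice** for a marketed cream. It can, but then the rating scale and the table must say so, and at present they do not.

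**Conclusion.** The point holds within these limits. For non-serious AEs other than local phototoxic reactions, the recording rule in 5.6.2 and 7.2.2 is incompatible with rating all AEs (7.2.3), with the *no* category (7.2.5) and with the tabulation in 8.2.3. One of the three relationship categories can hold only SAEs, a second has no clear recording rule, and the any-AE count is narrower than the AE definition. The number of missing events cannot be estimated from the Protocol.

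The conclusion assumes that sites follow 5.6.2 and 7.2.2 as written and that a phototoxic reaction is not rated *no*. It does not extend to a claim that the between-regime comparison is biased: the blinding status of the person rating relatedness is unstated, only the erythema and pustular eruption scores are explicitly planned by regime, and the main expected local reactions are captured. The correction should be made, because the loss cannot be recovered later and the change is cheap, but the point does not threaten the trial's primary conclusion.

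**What to change.** Remove the relatedness condition from 5.6.2 and 7.2.2. Require all AEs to be recorded over the period already set in 3.1 (first treatment until 3 months after the last), and have the relationship rated afterwards under 7.2.5. State in 7.2.5 whether the person giving that rating knows the regime.

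If restricted collection is intended, keep the condition but say so openly: state that *uncertain* events are recorded, and relabel the 8.2.3 table as treatment-related non-serious AEs plus all SAEs. The rating instruction in 7.2.3 should then be limited to match.

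The first option costs a wording change in two sections, a sentence on blinding, and extra CRF lines for minor unrelated events during the AE window. The second costs wording only, but gives up any count of non-serious AEs judged unrelated.

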### ***7.2.3 Assessment of Adverse Event***

Adverse events may be reported spontaneously by the subject or elicited through open (non-leading) questioning during the study. As far as possible, all AE's must be described by their duration (start and stop date), severity (mild, moderate, or severe; see Section 0), relationship to treatment (yes, uncertain, no; see Section 0), and according to the need of other specific therapy.

Localization of AE's will be recorded as "treatment area" or "non-treatment area"(see Section 0). The onset of AE's will be classified relative to the stage of treatment as described in Section 0.

### ***7.2.4 Severity of Adverse Event***

Adverse events will be graded as:

- Mild:           The AE is transient and easily tolerated.
- Moderate:    The AE causes the subject discomfort and interrupts the subject's usual activities.
- Severe:        The AE causes considerable interference with the subject's usual activities and may be incapacitating or life threatening.

### ***7.2.5 Relationship of Adverse Event to new treatment regime using MAL-PDT***

The investigator's opinion of the relationship of the AE(s) to the investigational drug, will be categorized as "yes," "uncertain," or "no."

- No: An AE, which after careful examination at the time of evaluation, is judged to be clearly and incontrovertibly due to extraneous causes (disease, environment, etc) and which does not meet the criteria for drug relationship and/or device relationship listed under uncertain or yes.
- Uncertain: An AE, for which after careful examination at the time of evaluation, the connection with the test drug administration or illumination appears unlikely, but cannot be ruled out with certainty.
- Yes: An AE, for which after careful examination at the time of evaluation, the connection to the test drug administration or illumination appears, with a high degree of certainty, to be related to the test drug and/or device.

### ***7.2.6 Localization of Adverse Events***

The investigator should report localization for all AE. For any local phototoxic reaction it must be reported if the adverse event occurred in the treatment area or not.

### ***7.2.7 Onset of Adverse Events***

The investigator will classify the onset of each AE relative to the following stages of treatment:

- After cream application and before light exposure
- During or immediately after light exposure
- After treatment

## **8. STATISTICAL EVALUATION**

### **8.1 Study Design**

Females and males above 18 years with primary and histologically verified BCC located outside of the mid-face (H-region) area with lesions of longest diameter of  $\leq$  than 15 mm when located in the face and on the scalp,  $\leq$  than 30 mm on the trunk and  $\leq$  than 20 mm on the extremities, will be included. This multi-centre study will be an open label, controlled blinded, randomized and parallel-group study where the lesions are randomized to either treatment by regime 1 or regime 2. Evaluation of efficacy and evaluation of cosmetic outcome will be assessed at the follow up visits; 3 12 and 36 months after last treatment. Adverse events will be noted at the 3-month follow-up after last treatment.

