## **1.2 Benefits and Risks**

Metvix® PDT is an approved and marked treatment modality for patients with pre-malignant disease and BCC.

General benefits of topical Metvix® PDT include:

- Non-invasive treatment available on an outpatient basis
- Several separate lesions can be treated simultaneously
- The same lesion(s) can be treated repeatedly with success
- Excellent cosmetic results
- No known toxicity or interaction with other medication
- Lesion selective, leaving the surrounding tissue intact
- No skin photosensitization after 24 hours
- Only minor, manageable local side effects related to treatment site

Study benefits include the following:

If the effect of the new, alternative and simpler treatment regime proves as effective as the standard approved regime MAL-PDT will be an even more attractive therapy alternative for low-risk BCC. The treatment will be easier to manage with improved cost-effectiveness as well as reduced discomfort and fewer side effects for the patients.

The risks attributed to Metvix® PDT are few and related mainly to transient discomfort and pain during and shortly after illumination. Inflammation following tumour destruction may give local, transient erythema and oedema. Treatment of large lesions may cause severe erythema, followed by ulceration. These side effects normally last for a few days, in rare occasions up to a week after treatment.

Standard Metvix® PDT in BCC is today given as two treatment sessions separated by one week. Patients with non-complete response after one PDT session in treatment regime 1 are offered an additional PDT at the 3-month control. The possible delay of the second session of BCC treatment is acceptable, as BCC grows very slowly

Patients with non-complete response after either PDT treatment regimes at the control visit 3 months after the latest treatment session are withdrawn from the study. They are then offered standard BCC treatment at the discretion of the dermatologist. Patients will receive detailed oral and written information about the risks of side effects. If the patients find the side effects unacceptable, they are free to withdraw from the study at any time and without any further explanation.

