### **10.3 Side effects**

PDT with two sessions of Metvix® is an approved, marketed treatment of patients with BCC. PDT might be associated with local discomfort or pain during illumination and to a lesser degree after treatment. Inflammation and erythema can also be seen in the treatment area after PDT and when treating skin with severe lesions severe erythema and crusting will be expected. These side effects will disappear during a few days and in rare cases up to one week after treatment. Systemic adverse events are not suspected.

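### The protocol places adverse event recording 11 to 13 weeks after each session, in conflict with its own requirements for timing and scoring of local reactions that last days

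*Protocol*

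**What the plan says.** **When events are recorded.** Section 8.1 fixes the time: "Adverse events will be noted at the 3-month follow-up after last treatment". Section 5.6.2 agrees: "Adverse event will be recorded in the CRF at the follow-up visits if related to treatment, according to the investigator". For events between visits it points the patient elsewhere: "In case of any adverse event patients should take contact with their G.P. or the local hospital for further consultation". Table 1 has an adverse event row with two marks, one of them tagged III, the schedule for re-treated regime 1 lesions.

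**How long reactions last.** Section 1.2: "These side effects normally last for a few days, in rare occasions up to a week after treatment". Section 10.3 agrees: "These side effects will disappear during a few days and in rare cases up to one week after treatment".

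**What must be captured.**
- Section 7.2.2 sends pain, erythema, pustular eruption and other treatment-related events to the CRF, and names no visit.
- Section 7.2.3 asks, as far as possible, for start and stop dates and severity.
- Section 7.2.7 asks for onset in three classes: between cream and light, during or just after light, or later.
- Section 8.2.3 commits to a tabulation: "The erythema and pustular eruption scores with 4 categories will be summarized by treatment regime group and time point using count and percent".

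Section 3.1 sets the reporting window for both regimes as the start of treatment to 3 months after the last treatment.

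**The concern.** A reaction that has cleared within a week cannot be graded by inspection at a visit some three months later. Nor can its start, its stop, or its onset relative to illumination be observed then. An investigator who follows 8.1 and 5.6.2 literally can fill these fields only from what the patient remembers.

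Attribution is a further difficulty. Section 4.1 plans 374 lesions in 277 patients, and section 5.2 gives successive lesions in one patient alternating regimes. Some patients would have to recall which site reacted after which session.

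At stake is the descriptive comparison of tolerability. Section 1.2 gives less discomfort and fewer side effects as part of the rationale for the simpler regime. If short-lived reactions are under-recorded, a real difference in treatment burden may not show. No later analysis can recover reactions that were not recorded when they occurred.

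**Working it through.** **Step 1: where the Table 1 marks fall.** The visit columns are 1, 1b, 2, 2b, 3 and 4. As extracted, the clinical assessment row has marks under 1b, 2 (tagged III), 2b and 3. That would leave the 3-year visit without an assessment and put the tagged mark before the re-treatment follow-up. Moving the row one column to the right gives visits 2, 2b (tagged III), 3 and 4, which matches the follow-up table in 5.6.2. The same shift puts the two adverse event marks on visits 2 and 2b. This is the likely reading; the broken table cannot confirm it. On this reading there is no mark at visit 1 or 1b.

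**Step 2: interval from session to recording.** Interval = week of the recording visit minus week of the session, both from Table 1.

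| Schedule | Session week | Recording week | Interval (weeks) |
|---|---|---|---|
| I (regime 2), first session | 1 | 14 | 14 − 1 = 13 |
| I (regime 2), second session | 2 | 14 | 14 − 2 = 12 |
| II (regime 1, single session) | 1 | 12 | 12 − 1 = 11 |
| III (regime 1), first session | 1 | 12 | 12 − 1 = 11 |
| III (regime 1), re-treatment | 12 | 24 | 24 − 12 = 12 |

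The range is 11 to 13 weeks. This agrees with the stated 3 months: 3 × 365.25/12 ÷ 7 = 13.0 weeks.

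**Step 3: interval from resolution to recording.** Take one week, the duration that 1.2 and 10.3 call rare, and subtract it from each interval. The results are 12 and 11 weeks for schedule I, 10 for schedule II, and 10 and 11 for schedule III. A reaction that lasts a full week has therefore been gone for 10 to 12 weeks when the scheduled recording takes place. A shorter reaction has been gone for longer.

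**Step 4: requirements against timing.**

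| Requirement | Can it be observed 11 to 13 weeks later? |
|---|---|
| Pain, erythema, pustular eruption (7.2.2) | Only if persistent |
| Start and stop dates (7.2.3) | By recall |
| Onset relative to light (7.2.7) | By recall |
| Four-category scores by regime and time point (8.2.3) | Only for what remains |

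The 8.2.3 scores cannot be rebuilt from adverse event severity either, because 7.2.4 has three grades and the scores have four categories.

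**The case against.** The strongest reply is that 8.1 does not say that events are noted only at 3 months, and that other sections point to capture at the session. Section 7.2.2 restricts recording to no visit. Section 7.2.3 allows spontaneous or elicited reports during the study. Section 7.2.7 has onset classes that fit the treatment day. Section 8.2.3 refers to time points. Section 7.2.1 registers events between consent and treatment as baseline symptoms, so something is captured at visit 1 without a mark in Table 1. Clinic staff perform the whole treatment (5.7) and could see the reactions. This stands in part: it makes the defect a conflict between sections and not proof that session data will be absent. It does not remove the defect, because only 8.1, 5.6.2 and Table 1 name visits, and the visits they name are follow-up visits. With nine centres intended, practice could differ between them.

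A reader might infer more than the protocol supports:
- **That no adverse event mark falls on a treatment visit.** Visit 2 is also the regime 1 re-treatment visit, so on the likely reading one mark does. Table 1 does not say whether that mark covers the session given that day.
- **That visit 1b makes ascertainment unequal.** If nothing is recorded at 1b, that visit creates no recorded difference. If something is, first-session reactions in regime 2 do not depend on late recall. The two arguments cannot be used together.
- **That the difference in session numbers measures the problem.** With 187 lesions per arm, regime 2 has 187 × 2 = 374 sessions and regime 1 has 187 × (1 + r), a reduction of (1 − r)/2. The re-treatment fraction r is not given. Assumed values of 10% to 50% give reductions of 45% to 25%. This contrast does not depend on when events are recorded.
- **That the CRF has no session-level fields.** The CRF is not available, so this cannot be known.

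**Conclusion.** The concern holds as a conflict on timing. The sections that name visits put recording 11 to 13 weeks after each session, while the sections that define the content ask for information that, for reactions lasting days, exists only at the session or shortly after it.

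If 8.1 and 5.6.2 are followed as written, the by-regime summary of non-serious local reactions would rest largely on recall and would probably under-report them. The extent of under-reporting cannot be calculated from the protocol. It would go too far to say that the summary must rest on recall alone, or that the scores will be near zero in both arms, because that assumes no centre records at the session.

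The scope is limited. The planned comparison is a descriptive tabulation with no safety hypothesis. Serious adverse events are outside the problem, since 7.1.2 requires reporting within 24 hours of the investigator's knowledge. Persistent and late events can still be seen at 3 months.

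The conclusion assumes the shifted-column reading of Table 1 and the durations in 1.2 and 10.3. Those durations are described as usual and not as upper limits: 1.2 also mentions severe erythema followed by ulceration in large lesions. The conflict between 8.1 and 5.6.2 on one side and section 7.2 and 8.2.3 on the other does not depend on the Table 1 reading.

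**What to change.** Amend 5.6.2, 8.1 and Table 1 so that they agree with section 7.2 and 8.2.3:

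1. Score pain, erythema and pustular eruption per lesion on the CRF at each treatment session: visit 1, visit 1b, and the regime 1 re-treatment at visit 2. Take the visit 1 scores before the allocation is revealed. Sections 3.3 and 5.2 already place randomization after illumination, so these scores cannot be influenced by knowledge of the regime.
2. Keep the 3-month visits for persistent and late events.
3. Tabulate the 8.2.3 scores by session.
4. Only regime 2 returns at one week. If reactions since the first session are recorded at visit 1b, report them separately and do not compare them between regimes.

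The sessions already take place, and only measurement changes. The cost is a few minutes per session, a Table 1 edit and a CRF block if the CRF does not already have one.
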